### Data collection

For each randomized patient a specially designed digital Case Report Form (CRF) will be completed. The CRF consists of a sequential set of instructions with provision for data recording. Internet-based remote data capture will be used for entering, managing and validating data from the investigative sites. For this purpose Oracle Clinical will be used, a program designed to meet industry regulations, including FDA 21CFR Part 11 Rule (March 20, 1997), ICH; Good Clinical Practice: Consolidated Guideline (May 9, 1997) and FDA Guidance for Industry "Computerized Systems Used In Clinical Trials" (May 10, 1999).

All randomized patients are identified by a Patient Identification Number (PIN) in combination with a center number. Trial personnel will not pass names outside the local hospitals. The investigator will ensure that patients' anonymity is maintained. On CRFs or other documents submitted to the coordinating center, patients will not be identified by their names but by a PIN in combination with a center number. The subject identification code list will be safeguarded by the investigator.

### Data acquisition and follow-up

Participating patients will be assessed at the following time points (Table 2):

**Table 2 T2:** Patient assessment.

	Physician									Patient			
	
	Baseline characteristics*	Sport resumption	Work resumption	AAS	AOFAS-AHS	CT	Wound inspection	Compliance	Adverse events	FAOS	EQ-5D	NRS pain	NRS satisfaction
**Preoperative**	X			X	X	X				X	X	X	

**1–2 weeks**							X	X	X				

**1 month**			X					X	X		X	X	X

**2 months**		X	X	X	X		X	X	X	X	X	X	X

**6 months**		X	X	X							X	X	

**1 year**		X	X	X	X	X			X	X	X	X	X

* Baseline characteristics include age, gender, weight, height, affected side, duration of symptoms, type of sport and profession, past medical history, smoking status, and size, localization and classification of osteochondral defect on computed tomography.

AAS = Ankle Activity Score; AOFAS-AHS = American Orthopaedic Foot and Ankle Society – Ankle-Hindfoot Scale; CT = Computed Tomography; FAOS = Foot and Ankle Outcome Score; EQ-5D = EuroQol questionnaire; NRS = Numeric Rating Scale.

1. *Preoperatively*: information letter, informed consent, baseline characteristics (age, gender, weight, height, affected side, duration of symptoms, past medical history, smoking status), type of sport and profession, AAS (2×: before symptoms and at preoperative assessment), AOFAS-AHS, FAOS, EQ-5D, NRS pain (2×: at rest and when running), CT: size, localization and classification of the OD (Table 3) [52]

**Table 3 T3:** Computed tomography classification of osteochondral defects of the talus [52].

Grade	Description
I	Compression
II	Partially fractured but undisplaced
III	Completely fractured but undisplaced
IV	Displaced fracture
V	Radiolucent (fibrous) defect

2. *1–2 weeks postoperatively*: check compliance, (S)AEs, wound inspection (healing, signs of infection)

3. *1 month postoperatively*: check compliance, (S)AEs, resumption of work, EQ-5D, NRS pain (at rest) and satisfaction

4. *2 months postoperatively*: check compliance, (S)AEs, resumption of sport and work, AAS, AOFAS-AHS, FAOS, EQ-5D, NRS pain (at rest and when running, if applicable) and satisfaction, wound inspection, stop PEMF- or sham-treatment

5. *6 months postoperatively*: resumption and maintenance of sport and work, AAS, EQ-5D, NRS pain (at rest and when running)

6. *1 year postoperatively*: resumption and maintenance of sport and work, AAS, AOFAS-AHS, FAOS, EQ-5D, NRS pain (at rest and when running) and satisfaction, (S)AEs, CT: subchondral plate and bone volume filling

### Recording sport resumption

To assess the resumption of sports and work, the patients will keep a diary that will be supplied at inclusion. Every time they perform sports they will record the type of sport and activity level (i.e., professional, competitive, or recreational) in this diary. They will also record the resumption of work, as defined above. This diary will be used for the monitoring of resumption and maintenance of sports and activity levels. At the postoperative visits the patients will be asked to check their diaries and report their sport activities and work resumption, to be filled out on the CRF. At one year the diary will be collected for assessment and confirmation of resumption dates.

### Sample size

Our sample size calculation is based on the combined primary endpoints (a) number of patients that resume and maintain sports during 12 months follow-up, and (b) the time to resumption of sport. Based on our experience it is expected that 50% of patients will resume and maintain sports within one year after the surgical intervention. Offering additional PEMF-treatment, we aim to improve this outcome to 75%. Of the patients who resume to sport the mean time to return to sports after debridement and microfracturing is 15 (standard deviation, 4 weeks) [4]. We consider a 20% reduction in time to return to sports as clinically relevant, i.e., 3 weeks. A sample size of 30 patients in each group (60 patients in total) will have 80% power to detect a joint difference (control group proportion of 0.50 versus treatment proportion of 0.75; control group mean of 15 weeks versus treatment group mean of 12, assuming a common standard deviation of 4), using a Fisher's combination test with a 0.05 two-sided significance level. In reported clinical trials with this device 9% to 13% of included patients dropped out [28,38]. Therefore, 34 patients will be included in each treatment group (68 patients in total).

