### Statistical methods

The following baseline characteristics will be summarized using descriptive statistics: number of patients, gender, age, affected side, duration of symptoms (months), prior ankle surgery, body mass index (kg/m^2^), trauma, smoking, size of lesion (mm), classification, duration of PEMF- or sham-treatment (hours), AAS, NRS pain, FAOS, AOFAS-AHS, and EQ-5D. Continuous data will be presented as mean and standard deviation if normally distributed, or as median and range in case of skewed distribution.

The main analysis of this trial consists of a comparison between the treatment groups of the primary outcomes: number of patients who resume and maintain sports and the time to resumption of sport (of the patients who resume sport). The number of patients who resume sport will be analyzed using the two group *X*^2 ^test, whereas the difference in mean weeks to sport resumption will be analyzed by a two group Student's *t*-test. Both *p*-values will be combined using the Fisher's combination test. Kaplan-Meier survival curves and the log-rank test will also be used for comparing time to resumption of sport. The stratification variables will be included in the primary analysis.

The repeated datastructure of the secondary outcomes (AAS, AOFAS-AHS, FAOS, EQ-5D, NRS-pain, and NRS-satisfaction) will be analyzed with linear mixed models, including a time-treatment interaction effect. The number of adverse events and time to resumption of work will be analyzed using a *Χ*^2 ^test or log-rank test, when appropriate. Analyses will be based on the intention-to-treat principle and performed in SPSS. Statistical uncertainty will be quantified via 95% confidence intervals.

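### The primary Fisher combination uses p-values without direction, so opposed effects on the two components reinforce each other and a significant result need not support the trial's hypothesis

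*Protocol article*

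**What the plan says.** The article's Sample size section plans 30 patients per group for 80% power "using a Fisher's combination test with a 0.05 two-sided significance level". The alternative is 0.50 v 0.75 resuming and mean times of 15 v 12 weeks with a common SD of 4.

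The Statistical methods section names the components. "The number of patients who resume sport will be analyzed using the two group" chi-square test, and "the difference in mean weeks to sport resumption will be analyzed by a two group Student's" t-test. The second comparison is restricted to resumers: the outcome is given as "the time to resumption of sport (of the patients who resume sport", in brackets. Then: "Both *p*-values will be combined using the Fisher's combination test".

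The Abstract and the study question at the end of the Background are directional on both components: patients on PEMF should return sooner, and more of them should return. Neither statistical section uses a one-sided component p-value, asks for the two effects to agree in sign, or says how opposed effects would be read.

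**The concern.** Fisher's statistic, −2(ln p₁ + ln p₂), grows as either p-value shrinks, whichever arm the effect favours. If more PEMF patients resume but PEMF resumers are slower, or the reverse, the two pieces of evidence add up instead of offsetting each other. The trial could then report a significant primary result on components that contradict each other, although its question is about benefit on both.

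Such a pattern is possible here because time is compared among resumers only. A device that brought back patients who would otherwise not have resumed, and who return late, would raise the proportion and lengthen the mean time together.

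**Working it through.** **Inputs.** From Sample size: 30 per arm, 0.50 v 0.75 resuming, 15 v 12 weeks, SD 4, level 0.05 two-sided. From Statistical methods: chi-square test, t-test among resumers, Fisher's combination. The simulations assume normal times, an uncorrected chi-square test unless stated, and no adjustment for the stratification variables. The 5% critical value on 4 df is 9.49.

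**1. The plan's own figure.** Simulated power with unsigned p-values is 0.780 (chi-square and t). It is 0.790 with an unpooled z for the proportions, 0.802 with z for both components, and 0.720 with a continuity correction. The stated 80% is essentially reproduced.

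**2. One worked data set.** Take 15/30 v 22/30 resuming and a 3-week difference in means.
- Pooled proportion 37/60 = 0.617; z = 0.233/√(0.617 × 0.383 × 2/30) = 1.86; p = 0.063.
- t = 3/(4√(1/15 + 1/22)) = 2.24 on 35 df; p = 0.032.
- Fisher: −2(ln 0.0631 + ln 0.0316) = 12.44; p = 0.014.

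This p = 0.014 is the same whether PEMF resumers return 3 weeks sooner or 3 weeks later. With one-sided p-values, the concordant case gives −2(ln 0.0315 + ln 0.0158) = 15.21, p = 0.004. The opposed case gives p = 0.139 towards benefit (0.0315 and 0.984) and p = 0.079 towards harm (0.968 and 0.0158). Neither reaches 0.025.

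**3. Rejection rates, 30 per arm.**

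| Truth (sham v PEMF) | Rule as written | Share of rejections with opposed signs |
|---|---|---|
| 50% v 75%, 15 v 12 weeks (the plan) | 78% | about 1% |
| 50% v 75%, 15 v 18 weeks | 78% | 98% |
| 75% v 50%, 15 v 12 weeks | 78% | 98% |
| No effect on either | 5.1% | 49% |

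**4. Late extra resumers (an assumption; the article gives no such figure).** Suppose PEMF speeds nobody up and the additional 25% of patients resume late. The PEMF mean is (50 × 15 + 25 × L)/75, where L is their return time.

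| L (weeks) | PEMF mean (weeks) | Significant | Of these, opposed |
|---|---|---|---|
| 16 | 15.3 | about 42% | about 62% |
| 18 | 16.0 | about 47% | about 81% |
| 20 | 16.7 | about 53% | 91% to 92% |
| 24 | 18.0 | about 67% | 97% to 98% |

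If instead the usual resumers do speed up by the planned 3 weeks and the extra ones return at 18 weeks, about 45% of trials are significant and about 20% of those are opposed.

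**5. The remedy, in two steps.** Directional p-values at 0.025 give planned power of 83%. They do not settle the matter alone. With 50% v 75% and 15 v 18 weeks they still claim benefit in about 26% of trials and harm in about 31%. About 7% claim both at once, so 26 + 31 − 7 = 50% reject in some direction. If both estimates must also favour the same arm, benefit claims there fall to 26.2% − 25.5% = about 0.6%. In the reverse case (75% v 50%, 15 v 12 weeks) they fall from 30.8% to about 1.3%. Planned power becomes about 82%. Under the null, each tail rejects in about 2.5% − 0.5% = 2%.

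**The case against.** The strongest reply is that the test is valid. Against the global null it rejects in about 5% of trials, and a half share of discordant false positives is simply what independent two-sided components produce. A reader might infer an inflated error rate; the calculation does not support that. Under the plan's own alternative, only about 1% of significant results are opposed. A reader might also infer that the trial is undersized, but the stated 80% is essentially met as written.

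Statistical methods also compares the components separately, adds Kaplan-Meier curves and a log-rank test, and promises 95% confidence intervals. Opposed effects would therefore be visible. It would go too far to say that the report could not show which arm did better on each component. This limits the harm but leaves the combined decision rule unchanged.

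A reader might take opposed effects to be likely. The article supports only that they are possible: the late-resumer scenarios have no source in it, and the 24-week value lies 9 weeks, or 2.25 SD, beyond the sham mean. Late extra resumers would also disturb the resumers-only time comparison under any combination rule.

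Finally, the article does not expressly call the component p-values two-sided, and a fuller analysis plan could fix a sign convention. The power figure does not decide this, since directional p-values with a continuity correction give 0.784. The wording does point one way: a two-group chi-square test, a two-group t-test, a two-sided level, and no one-sided language.

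**Conclusion.** The point stands as a fault in the meaning of the primary result. The rule cannot distinguish the hypothesised benefit from a mixed result: it rejects in about 78% of trials for 15 v 12 and for 15 v 18 weeks alike. A significant combination would therefore not answer the study question by itself. Type I error and sample size are not in question.

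The 78% figures rest on the plan's own proportions and SD, normal times and an uncorrected chi-square test. The late-resumer figures (42% to 67% significant, 62% to 98% of those opposed) rest on assumed return times and show what could happen, without saying how probable it is.

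**What to change.** Amend Sample size and Statistical methods by two sentences, before unblinding:

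1. Compute both component p-values one-sided towards PEMF benefit (signed root of the chi-square; one-sided t), combine them on chi-square with 4 df, and reject at 0.025. Do the mirror test towards sham at 0.025.
2. Claim superiority of an arm only if both component estimates favour that arm. Otherwise report the components separately, without a primary claim.

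No extra patients are needed: planned power at 30 per arm is about 82%, against 78% as written and 83% without the second condition. The overall level stays at or below about 5%.

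The price is that one very strong component beside an opposed second one no longer counts as a primary success. If PEMF truly changed only the proportion, the chance of a primary claim would fall from about 41% to 39.4% − 14.5% = about 25%. If it changed only the time, the chance would fall from about 39% to 36.6% − 11.4% = about 25%. That fits a hypothesis of benefit on both, but the sponsor should accept it knowingly.

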### Statistical methods

The following baseline characteristics will be summarized using descriptive statistics: number of patients, gender, age, affected side, duration of symptoms (months), prior ankle surgery, body mass index (kg/m^2^), trauma, smoking, size of lesion (mm), classification, duration of PEMF- or sham-treatment (hours), AAS, NRS pain, FAOS, AOFAS-AHS, and EQ-5D. Continuous data will be presented as mean and standard deviation if normally distributed, or as median and range in case of skewed distribution.

The main analysis of this trial consists of a comparison between the treatment groups of the primary outcomes: number of patients who resume and maintain sports and the time to resumption of sport (of the patients who resume sport). The number of patients who resume sport will be analyzed using the two group *X*^2 ^test, whereas the difference in mean weeks to sport resumption will be analyzed by a two group Student's *t*-test. Both *p*-values will be combined using the Fisher's combination test. Kaplan-Meier survival curves and the log-rank test will also be used for comparing time to resumption of sport. The stratification variables will be included in the primary analysis.

The repeated datastructure of the secondary outcomes (AAS, AOFAS-AHS, FAOS, EQ-5D, NRS-pain, and NRS-satisfaction) will be analyzed with linear mixed models, including a time-treatment interaction effect. The number of adverse events and time to resumption of work will be analyzed using a *Χ*^2 ^test or log-rank test, when appropriate. Analyses will be based on the intention-to-treat principle and performed in SPSS. Statistical uncertainty will be quantified via 95% confidence intervals.

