**Methods/Design:**

A prospective, double-blind, randomized, placebo-controlled trial (RCT) will be conducted in five centers throughout the Netherlands and Belgium. 68 patients will be randomized to either active PEMF-treatment or sham-treatment for 60 days, four hours daily. They will be followed-up for one year. The combined primary outcome measures are (a) the percentage of patients that resume and maintain sports, and (b) the time to resumption of sports, defined by the Ankle Activity Score. Secondary outcome measures include resumption of work, subjective and objective scoring systems (American Orthopaedic Foot and Ankle Society – Ankle-Hindfoot Scale, Foot Ankle Outcome Score, Numeric Rating Scales of pain and satisfaction, EuroQol-5D), and computed tomography. Time to resumption of sports will be analyzed using Kaplan-Meier curves and log-rank tests.

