Clinically, its favorable effects are less obvious. PEMF as a solitary treatment for osteoarthritis of the knee has been repeatedly investigated, with conflicting results [7,22-25]. Although the effect of PEMFs on osteoarthritis of the knee seems equivocal, their value in the additional treatment of other bony and cartilaginous pathologies is promising. PEMFs have been proven as a successful method in fracture healing, especially in the case of non-union [8,26,27]. PEMF-treatment also favors the recovery of patients after arthroscopic treatment of chondral lesions in the knee, and reduces the use of non-steroidal anti-inflammatory drugs [28]. To our knowledge, sport resumption with the use of PEMFs has not been investigated. Based on the above data, we believe that PEMFs may act on ODs by improving bone regeneration and suppressing inflammation evoked by surgery.

When the above results are combined, it seems justified to state that additional PEMF-treatment may contribute to the management of ODs. Our study question is: "Does treatment with PEMFs compared to sham device lead to earlier resumption of sports in a higher percentage of patients with an osteochondral defect of the talus after arthroscopic debridement and microfracturing?".

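### Fisher's combination test on two-sided p-values can reject on one component, or on components pointing opposite ways, so a positive primary result does not by itself answer the study question; the log-rank test also has no stated role

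*Protocol article*

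**What the plan says.** **Question.** The Background asks whether PEMF, compared with sham, will "lead to earlier resumption of sports in a higher percentage of patients". That names both components, each in the favourable direction.

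**Main analysis.** Under Statistical methods, the number who resume is compared by a chi-square test and the mean weeks to resumption, among resumers, by Student's t-test. The two p-values are combined by Fisher's test. The same paragraph continues: "Kaplan-Meier survival curves and the log-rank test will also be used for comparing time to resumption of sport".

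**Sample size.** Thirty patients per group "will have 80% power to detect a joint difference", namely "control group proportion of 0.50 versus treatment proportion of 0.75" together with 15 versus 12 weeks (SD 4), "using a Fisher's combination test with a 0.05 two-sided significance level".

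**Abstract (Methods/Design).** The only test named for the primary outcome is the log-rank: "Time to resumption of sports will be analyzed using Kaplan-Meier curves and log-rank tests". Fisher's test is not mentioned.

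**The concern.** Fisher's test addresses one hypothesis: that neither component differs between the arms. Rejecting it shows a difference somewhere. It does not show that both components differ. With two-sided p-values it also carries no information on whether the components agree in direction. The study question asks for benefit on both, and the sample-size section calls the target a joint difference. A reader could therefore take a positive Fisher test as the answer to the whole question when one component, or two conflicting ones, produced it.

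The second matter is the log-rank test. It concerns the same primary outcome and, as usually applied, keeps non-resumers as censored, whereas the t-test leaves them out. The two analyses can therefore disagree. The protocol does not call log-rank supportive, and the abstract makes it look like the principal test.

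**Working it through.** **Inputs.** From Sample size: 30 per arm, 0.50 versus 0.75 resuming, 15 versus 12 weeks, SD 4, two-sided 0.05. From Statistical methods: the t-test uses resumers only, so about 15 (30 × 0.50) versus 22.5 (30 × 0.75) patients are expected.

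**Assumptions.** Normally distributed times, uncorrected chi-square, no adjustment for stratification variables, no dropout, and non-resumers censored at 52 weeks for log-rank. Main run: 200,000 simulated trials per scenario.

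**Test rule.** X = −2(ln p₁ + ln p₂), referred to chi-square with 4 degrees of freedom. The tail probability is exp(−X/2)(1 + X/2), and the 5% critical value is 9.488. Rejection therefore needs p₁ × p₂ ≤ exp(−4.744) = 0.0087. Three consequences follow:
- One component with p ≤ 0.0087 is enough, whatever the other shows.
- Two components each at p = 0.09 also reject (0.09 × 0.09 = 0.0081), although neither is significant alone.
- Two components each at p = 0.05 give X = 11.98 and a combined p of 0.0025 × 6.99 = 0.017. Significance on both therefore always implies a Fisher rejection.

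**The plan's own figure.** Fisher power is 78.0% at 30 per arm, 79.5% at 31 and 80.7% at 32. The stated 80% is reproduced to within two patients per arm. With no effect on either component, Fisher rejects 5.2% of the time.

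**What a rejection means, at 30 per arm**

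| True effects | Fisher rejects | Log-rank rejects |
|---|---|---|
| None | 5.2% | 5.1% |
| Design effects on both | 78.0% | 73.0% |
| Time only (15 to 12 weeks) | 38.6% | 7.0% |
| Proportion only (0.50 to 0.75) | 41.5% | 49.3% |
| Opposite (0.50 to 0.75, but 15 to 18 weeks) | 78.0% | 27.7% |

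The second and last rows have the same Fisher figure because two-sided p-values ignore sign.

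**Both components separately.** At the design effects, power is 51.8% for chi-square and 58.4% for the t-test. Both are at or below 0.05 in 29.4% of trials (the simple product, 0.518 × 0.584, is 0.30). Of the Fisher rejections, 0.294 / 0.780 = 38% have both components significant.

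**Fisher against log-rank.** At the design effects they disagree in 9.6% (Fisher only) + 4.6% (log-rank only) = 14.2% of trials. With no effect, at least one of them rejects in 7.8%.

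**The case against.** The strongest reply is that the design is coherent as stated. The sample-size section ties both the 5% and the 80% to one named test, and both figures reproduce. Statistical methods places that test in the main analysis. The word *also* before log-rank most naturally marks it as additional, and log-rank is nowhere linked to the significance level or the power. The abstract is a summary naming a method for one component. The study question is narrative, not a decision rule, and labels for supportive analyses may stand in a statistical analysis plan that is not shown.

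Much of this stands. A reader might infer that the 5% level and the 80% power are wrong. The documents do not support that, because both figures are given for Fisher's test and hold for it. The 7.8% applies only if either test could count as success, and the 30% only if a joint difference means separate significance on both components. The protocol states neither rule. Counting the chi-square and t-tests as further routes to success would go further still against the text, which uses them as inputs to Fisher's test.

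One thing is not answered. The primary rule as written can be positive with mixed or opposite effects while the question asks for consistent benefit. That lies in what the protocol states, not in detail left elsewhere. The abstract's omission of Fisher's test is likewise a difference between two printed passages.

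**Conclusion.** The point holds in limited form. The sample size and the significance level of Fisher's test are sound. What does not follow is the step from a Fisher rejection to the benefit named in the study question. The test rejects about 40% of the time when only one component has an effect, and about 78% when more patients resume but later. The unassigned log-rank test and the abstract add a smaller ambiguity: disagreement in about 14% of trials at the design effects and, only if either test were accepted as success, a false-positive rate of about 7.8%.

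These figures rest on the assumptions listed with the calculation. The algebra of the test, including its blindness to direction, does not depend on them. The matter should be settled before unblinding, since it decides what a positive result may be said to show.

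**What to change.** 1. Name Fisher's combination test, on which the trial is sized, as the sole confirmatory test. Label Kaplan-Meier and log-rank as supportive, and name Fisher's test in the abstract. (Making log-rank confirmatory instead would require a new sample-size calculation.)
2. Add a rule for component claims: benefit on a component is claimed only if the Fisher p-value and that component's own p-value are both at or below 0.05 and the effect favours PEMF. This is a closed test of two hypotheses and holds the family error at 5% without splitting it.
3. State that results in which the components point in opposite directions will be reported as mixed, not as a benefit. If Fisher rejects but neither component meets the rule, report only that some difference was found.
4. In Sample size, replace the joint-difference wording with *about 80% power to reject no difference in either component*, and note that power to show both separately is about 30% at 30 per arm.

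**Cost.** Wording only, with no extra patients and no loss of significance level. The downside is that the stated power for a claim on both components reads less favourably.

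### The secondary mixed models state no adjustment for preoperative scores already collected; adding it costs nothing and narrows the intervals, and satisfaction should be judged on the arm difference, not the interaction test

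*Protocol article*

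**What the plan says.** Statistical methods in the protocol article gives one specification for AAS, AOFAS-AHS, FAOS, EQ-5D, NRS pain and NRS satisfaction: they "will be analyzed with linear mixed models, including a time-treatment interaction effect". The interaction is the only model term named. The one sentence on covariates concerns another analysis: "The stratification variables will be included in the primary analysis". Otherwise, Statistical methods mentions preoperative scores only in the list of characteristics to be summarized descriptively. It promises 95% confidence intervals but does not say for which contrast.

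Data acquisition and follow-up shows which outcomes have a preoperative value. The preoperative visit records "AAS (2×: before symptoms and at preoperative assessment), AOFAS-AHS, FAOS, EQ-5D, NRS pain (2×: at rest and when running"; satisfaction is not listed there. Satisfaction first appears at 1 month ("resumption of work, EQ-5D, NRS pain (at rest) and satisfaction"), then at 2 months ("NRS pain (at rest and when running, if applicable) and satisfaction, wound inspection") and at 1 year ("NRS pain (at rest and when running) and satisfaction, (S)AEs"). Table 2 agrees.

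**The concern.** The same sentence covers two different data structures.

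- **Five outcomes with a preoperative value.** The natural reading of a repeated-measures model is that the preoperative visit is one of the repeated measurements. The interaction at a later visit then compares the arms on change from baseline. That comparison is valid under randomization, but less precise than one that adjusts for the baseline value.
- **Satisfaction.** All three measurements are postoperative. The interaction asks only whether the arm difference varies between them. If PEMF patients were more satisfied by the same amount throughout, the interaction would be zero.

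At stake is avoidable imprecision on secondary outcomes in a trial of 68 patients, and a possible misreading of the satisfaction result if the interaction p-value is taken as its treatment test.

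**Working it through.** **Inputs.** The article gives no numerical figure for the secondary models; its power statement concerns the combined primary endpoint and does not bear on this point. I use 30 evaluable patients per group (Sample size). The correlation rho between baseline and follow-up and the effect sizes are not in the article. I assume rho of 0.3, 0.5 and 0.7, and effects of 0.5 and 0.8 SD.

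**Step 1: outcomes with a preoperative value.** Take equal SDs (sigma) at baseline and follow-up, and n per group.

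- Interaction contrast at one visit, with baseline as an unconstrained repeated outcome: (arm difference at the visit) minus (arm difference at baseline). Variance = (2 sigma²/n) × 2(1 − rho).
- Baseline-adjusted difference at the same visit: variance = (2 sigma²/n) × (1 − rho²).
- Ratio, adjusted to change: (1 − rho²) / [2(1 − rho)] = (1 + rho)/2, which is below 1 for any rho below 1.

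Half-widths of the 95% interval in SD units are 1.96 × the square root of the variance. At rho = 0.5 they are 1.96 × √(2/30 × 1.00) = 0.506 for change and 1.96 × √(2/30 × 0.75) = 0.438 for the adjusted difference.

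| rho | change 2(1−rho) | adjusted 1−rho² | variance ratio | half-width, change | half-width, adjusted | interval narrower by |
|---|---|---|---|---|---|---|
| 0.3 | 1.40 | 0.91 | 0.65 | 0.599 | 0.483 | 19% |
| 0.5 | 1.00 | 0.75 | 0.75 | 0.506 | 0.438 | 13% |
| 0.7 | 0.60 | 0.51 | 0.85 | 0.392 | 0.361 | 8% |

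The last column is 1 − √ratio: √0.65 = 0.806, √0.75 = 0.866, √0.85 = 0.922. For an assumed 0.5 SD effect, power at a single visit is 37% (change) against 53% (adjusted) at rho 0.3, 49% against 61% at 0.5, and 71% against 77% at 0.7.

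If the preoperative value were not used at all, the half-width would be 0.506 at every rho. That is 5%, 15% and 40% wider than the adjusted interval at rho 0.3, 0.5 and 0.7. Adjustment gives the narrowest interval of the three.

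**Step 2: satisfaction.** Let d1, d2 and d3 be the arm differences at 1 month, 2 months and 1 year. The interaction test asks whether d2 − d1 = 0 and d3 − d1 = 0. If d1 = d2 = d3, both hold whatever the size of the benefit, so the test rejects only at its alpha. A simulation with 30 per group, three equally correlated visits and a constant benefit shows this, and also shows that the information is in the data:

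| constant benefit | rho between visits | interaction test rejects | visit-averaged difference rejects | 1-year difference rejects |
|---|---|---|---|---|
| 0.5 SD | 0.3 / 0.5 / 0.7 | 5% / 5% / 5% | 74% / 65% / 57% | 47% / 48% / 48% |
| 0.8 SD | 0.3 / 0.5 / 0.7 | 5% / 5% / 5% | 99% / 96% / 93% | 86% / 86% / 86% |

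The averaged and 1-year differences can both be taken from a model with time, treatment and their interaction.

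**The case against.** A reader might infer that the plan makes the interaction its sole treatment test in place of baseline adjustment, and that a steady satisfaction benefit would therefore be reported as no effect. The article does not support that. The word *including* names one term among others. It does not exclude a treatment main effect, visit-specific differences, a baseline covariate or a common baseline mean. The planned model can estimate a constant satisfaction benefit; only the interaction test cannot show it. The intention to give 95% confidence intervals suggests that estimates will be reported.

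Three further points are fair:

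- The article is condensed, and covariates and contrasts of secondary models are often left to an analysis plan. Silence alone is therefore no error.
- The precision loss in the table requires the preoperative visit to enter unconstrained. Its size depends on an assumed rho and shrinks as rho rises.
- The ratio (1 + rho)/2 describes a contrast at one visit with equal variances. It does not describe a joint interaction test over all visits: EQ-5D and NRS pain have five time points and AAS has four.

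These points limit the claim but do not remove it. The interaction is the only term the article names, no adjustment is stated for these models, and the preoperative values will be in hand. Adjusting for them is a concrete improvement to the stated model.

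**Conclusion.** The point holds as a free improvement, not as an error that threatens the trial. If the preoperative visit is an ordinary repeated outcome, the visit-specific interaction contrast for the five outcomes is less precise than a baseline-adjusted difference for any rho below 1. For an assumed rho of 0.3 to 0.7, adjustment leaves 0.65 to 0.85 of the variance and intervals about 8% to 19% narrower. For satisfaction, the interaction test on its own has power equal to its alpha against a constant benefit. That matters only if the test is used as the treatment test, which the article does not say. The change-based contrast is unbiased under randomization, and the primary analysis and sample size are untouched.

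**What to change.** In the wording for the secondary models:

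1. For AAS, AOFAS-AHS, FAOS, EQ-5D and NRS pain, model the postoperative visits with the preoperative value of the same outcome as a covariate, or keep the preoperative visit in the outcome vector and constrain the arms to a common baseline mean. AAS is recorded twice before surgery, so state which value is used.
2. Keep the time-treatment interaction so that the effect may differ by visit, and report the treatment difference with its 95% CI at each visit. Once only postoperative visits are modelled, the interaction test cannot show a constant benefit for these outcomes either, so the conclusion should rest on the differences.
3. For NRS satisfaction, base the conclusion on the treatment difference at each visit and averaged over the three visits, not on the interaction test.

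The cost is a few sentences in the analysis plan, with no new data or visits and no change to the primary analysis or sample size.
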